The primary aim of the present study is to assess whether adding lithium to standard therapy is an effective treatment strategy to reduce the risk of suicidal behaviour in long term treatment of people with TRD and previous history of DSH. Secondary aims of the study are: (a) to assess whether adding lithium has a specific impact in improving depressive symptoms; (b) to assess the long term tolerability profile of the lithium-augmentation strategy.

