## Methods/Design

In a multi-centre, 12-month, superiority trial, we will randomise patients with TRD and history of DSH to (i) add lithium to usual treatment (add-on lithium strategy) or (ii) avoid lithium in usual treatment (without-lithium strategy). To be as close as possible to clinical practice, patients and clinicians will not be blind to treatments provided during the trial. However, to limit the potential bias introduced by lack of blindness, an independent adjudicating committee, blind to treatment allocation, will validate the events that will constitute the primary outcome. Patients will be assessed at baseline before randomisation and then every month after random allocation until the completion of the 12-month follow-up. All phases of the trial will be recorded following the CONSORT statement [17,18].

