#### Inclusion criteria

(a) Diagnosis of major depression (clinical diagnosis, guided by DSM-IV criteria).

(b) An episode of DSH in the previous 12 months.

(c) Inadequate response to at least two antidepressants given sequentially at an adequate dose for an adequate time for the current depressive episode.

(d) Uncertainty about which treatment arm would be best for the participant.

(e) Age 18 or above.

(f) To sign written informed consent.

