### Baseline and follow up assessments

Before entering the study, patients will be asked to provide informed consent to participate. The following information will be collected at baseline: sociodemographic and clinical characteristics, diagnosis according to the Mini Neuropsychiatry Interview (MINI) [19], laboratory and electrocardiography (ECG) parameters, severity of illness according to the Quick Inventory Depression Scale (QIDS) [20], a self-rated instruments that has been shown to have good psychometric properties [21]. Detailed information will be gathered on previous DSH acts, as well.

Follow-up data will be obtained each month after random allocation using an electronic form, as follows: any death or DSH, lithium oral dose and plasma level (if applicable), concomitant drug treatments, QIDS scores, adverse events and information on laboratory and ECG parameters.

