### Outcomes

Suicide completion and acts of DSH during the 12 months of follow-up will constitute the composite primary outcome. The term “suicide” is defined as an act with a fatal outcome, deliberately initiated and performed by the person with the knowledge or expectation of its fatal outcome. DSH is defined as intentional self-poisoning or self-injury, irrespective of motivation, as the intention to end life may be absent or present to a variable degree [7,8]. To preserve outcome assessor blindness, an independent adjudicating committee (three clinical psychiatrists, with no links to the study and blind to treatment allocation) will anonymously review all deaths and all hazardous acts reported during the 12 months of follow-up by the treating clinicians. The committee will have the role of identifying, among deaths, the cases of suicide, and among hazardous acts those that constitute acts of DSH. Only the cases of suicide and those of DSH validated by the committee will constitute the primary outcome.

As secondary outcomes, we will consider number of events (acts of DSH), number of suicides and all-cause mortality, change in severity of depressive symptoms from baseline to endpoint and adverse reactions during the 12 months of follow-up.

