Time from randomised treatment assignment until all-cause mortality during the 12 months of follow-up will be analysed through a log-rank test for difference in survival between the two groups. The same method will be applied for the following secondary outcomes: suicide mortality, deliberate self-harm. Multivariate analyses will be performed to explore the possible role of prognostic factors on outcomes.

Change in severity of depressive symptoms from baseline to 12 months will be analysed as a continuous variable and as a dichotomous variables, where individuals showing an improvement of al least 50% will be considered treatment responders. Change in severity of illness at 12-months will be compared between the two groups of treatment through appropriate statistical methods for repeated measurements (paired t-test or McNemar non parametric test according to the variables distribution). The number of events/outcomes of interest (suicide or DSH) will be compared between the two groups of treatment through the chi-square test (or the Fisher’s exact test when appropriate). When possible, a multivariate analysis will be performed through a Poisson regression model with a robust error variance.

The proportion of patients with adverse reactions during the study will be compared between the two groups of treatment through the chi-square test (or the Fisher’s exact test when appropriate).

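### The depression outcome is compared without adjustment for baseline QIDS, which the trial already collects; adjusting is a nearly free gain in precision

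*Protocol article*

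**What the plan says.** The Background gives as secondary aim (a) "to assess whether adding lithium has a specific impact in improving depressive symptoms". The Outcomes section turns this into a secondary outcome, "change in severity of depressive symptoms from baseline to endpoint".

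The Statistical analysis section fixes the form of the analysis: "Change in severity of depressive symptoms from baseline to 12 months will be analysed as a continuous variable and as a dichotomous variables". Patients who improve by at least 50% "will be considered treatment responders". The tests named for comparing the two groups are "paired t-test or McNemar non parametric test according to the variables distribution". Neither accepts a covariate.

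The baseline score will be available. Methods/Design states "Patients will be assessed at baseline before randomisation and then every month after random allocation", and Baseline and follow up assessments lists QIDS among the baseline measures. Random allocation procedure stratifies by presence or absence of an Axis II diagnosis and by nothing else.

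Three other statements in Statistical analysis concern covariates:
- Gender and age are forced into the Cox model, which belongs to the primary outcome.
- A general sentence on exploring prognostic factors follows the survival outcomes and names no variable.
- A robust Poisson model, to be used when possible, follows the comparison of suicide and DSH events and names no variable.

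None commits to baseline QIDS for the depression outcome.

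**The concern.** Subtracting the baseline score does not adjust for it. Because of regression to the mean, patients who start higher tend to show larger raw falls. An arm that starts higher by chance is then credited with part of that difference as improvement. The same dependence adds noise to the arm comparison even when the arms happen to be balanced.

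Stratifying by Axis II diagnosis alone does not balance baseline severity by design, and the inclusion criteria set no minimum QIDS score, so baseline scores may be widely spread. At stake are the precision of the answer to secondary aim (a) and its robustness to an unlucky draw.

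**Working it through.** **Inputs.** From the documents: 105 patients per arm and a two-sided 5% level (Power analysis and sample size calculation), with 1:1 allocation. The article states no power or precision for the depression outcome, so there is no planned figure to reproduce. Assumed, because the documents do not give them: rho, the correlation of baseline with 12-month QIDS, and k, the 12-month SD divided by the baseline SD. The calculation also assumes no drop-out and a normal approximation. The comparator is a two-sample test on change, since the paired tests named in the plan do not compare independent arms.

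**Variances, in units of the baseline SD.**
- Change score: Vc = 1 + k² − 2·rho·k
- Adjusted for baseline: Va = k²(1 − rho²)
- Difference: Vc − Va = (1 − rho·k)². In large samples this is never negative, and it is zero when rho·k = 1.
- With k = 1: Vc = 2(1 − rho), Va = 1 − rho², and Va/Vc = (1 + rho)/2.

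**Power.** Take the effect that the change score detects with 80% power, δ = 2.80·√(2Vc/105). Adjusted power is then Φ(2.80/√(Va/Vc) − 1.96).

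| k | rho | Vc | Va | Va/Vc | adjusted power |
|---|---|---|---|---|---|
| 1 | 0.3 | 1.40 | 0.91 | 0.65 | 93.5% |
| 1 | 0.5 | 1.00 | 0.75 | 0.75 | 89.9% |
| 1 | 0.7 | 0.60 | 0.51 | 0.85 | 86.0% |
| 1.25 | 0.5 | 1.3125 | 1.1719 | 0.893 | 84.3% |
| 1.25 | 0.7 | 0.8125 | 0.7969 | 0.981 | 80.8% |
| 1.5 | 0.5 | 1.75 | 1.6875 | 0.964 | 81.4% |
| 1.5 | 0.7 | 1.15 | 1.1475 | 0.998 | 80.1% |

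For k = 1 and rho = 0.5, δ = 2.80 × √(2/105) = 2.80 × 0.138 = 0.387 SD.

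**Chance imbalance, k = 1 and rho = 0.5.**
- The standard error of the baseline difference is √(2/105) = 0.138 SD, so a 1.96-SE imbalance is 0.27 SD.
- The part that enters the change-score difference is (1 − rho) × 0.27 = 0.135 SD, in favour of the arm that started higher.
- The change-score test rejects beyond 1.96 × 0.138 = 0.271.
- Given the imbalance, the difference varies with SD √(2 × 0.75/105) = 0.120.
- The false-positive rate given that imbalance is Φ((0.135 − 0.271)/0.120) plus a negligible opposite tail, about 12.9%.
- The corresponding conditional rate at rho 0.5 is 8.4% for k = 1.25 and 6.2% for k = 1.5.

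**Simulation check, k = 1 and rho = 0.4, 4000 trials.** The SE of the arm difference was 0.151 for raw change and 0.126 adjusted. The slope of the estimate on the baseline imbalance was −0.61 for raw change (theory −0.60) and −0.01 adjusted.

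**The case against.** The strongest reply is that nothing here is invalid. Under randomisation, an unadjusted comparison of change is unbiased and holds its 5% level, so baseline adjustment is a matter of efficiency. That stands. A reader might infer from the 13% figure that the planned analysis is biased or has an inflated error rate. The documents do not support this: the figure applies only given an imbalance of 1.96 SE, which is reached or exceeded in about one trial in 20. Averaged over randomisations the rate is 5%.

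A second reply concerns size. A reader might take adjustment to be more precise at every rho below 1, or take the equal-SD figures as the expected gain. Neither follows. Wider spread at 12 months is plausible, because patients enter in a current episode after two failed antidepressants and may then diverge. The table shows how quickly the gain shrinks in that case. Carrying the last observation forward would also tend to raise rho, which reduces the gain when SDs are equal. This objection stands, and it is why the gain is given as a range.

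A third reply is that the general prognostic-factor sentence could cover baseline severity, and that covariate lists are often left to an analysis plan. This stands only in part. The sentence does not exclude baseline QIDS, but it is exploratory and is not the stated comparison. For that comparison the article itself chooses methods that cannot take a covariate.

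Finally, a 50% improvement is already expressed relative to baseline. How far it still depends on the starting score is not established here, and the figures above cover only the continuous outcome.

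**Conclusion.** The point holds as a free improvement, not as an error that invalidates the analysis. The stated comparison for secondary aim (a) leaves out a pre-randomisation measurement scheduled for every patient, and no other statement commits to using it.

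For the continuous outcome, adjustment raises 80% power to between about 86% and 93.5% if SDs are equal and rho lies between 0.3 and 0.7. The figures are about 84% and 81% (rho 0.5 and 0.7) if the 12-month SD is 1.25 times the baseline SD, and the gain can be close to zero. In large samples it is never negative. Adjustment also removes the carry-over of chance baseline imbalance. All of this rests on assumed values of rho and the SD ratio. The gain for the responder outcome is not quantified, and the primary time-to-event analysis is unaffected.

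The paired t-test and McNemar wording is a separate fault. Replacing it with an unpaired test on change would leave this point open.

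**What to change.** In Statistical analysis, make the between-arm comparison of depression a linear model of 12-month QIDS (or its change) on treatment with baseline QIDS as a covariate. Report the adjusted mean difference with its 95% CI. For response, use a robust Poisson model, a method the section already names, with treatment and baseline QIDS, and report the adjusted risk ratio. Show the unadjusted figures descriptively. The same rewrite should replace the paired t-test and McNemar wording.

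The cost is one or two sentences, one degree of freedom and a linearity assumption for one covariate. No further data, patients or visits are needed. Naming the covariate in advance also removes a later choice between adjusted and unadjusted results, which is worth having in an open-label trial with a self-rated scale.

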**Methods/Design:**

We will carry out a randomised, parallel group, assessor-blinded superiority clinical trial. Adults with a diagnosis of major depression, an episode of DSH in the previous 12 months and inadequate response to at least two antidepressants given sequentially at an adequate dose for an adequate time for the current depressive episode will be allocated to add lithium to current therapy (intervention arm) or not (control arm). Following randomisation, treatment is to be taken daily for 1 year unless some clear reason to stop develops. Suicide completion and acts of DSH during the 12 months of follow-up will constitute the composite primary outcome. To preserve outcome assessor blindness, an independent adjudicating committee, blind to treatment allocation, will anonymously review all outcome events.

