### Random allocation procedure

Patients will be randomly assigned to one of the two treatment groups with an equal probability of assignment to each treatment (allocation ratio 1:1). A centralised randomisation procedure will be employed. The trial biostatistician will prepare the sequence of treatments randomly permuted in blocks of unequal size. The allocation will be stratified by presence or absence of Axis II diagnosis *(patients with unipolar major depression AND personality disorder vs patients with unipolar major depression WITHOUT personality disorder)* because this variable may have an impact on the study outcomes (see Discussion).The randomisation schedule will be generated using nQuery Advisor, release 7.0. Recruiting physicians will contact an administrator at the World Health Organisation Collaborative Centre for Research and Training in Mental Health and Service Evaluation of the University of Verona who will access a computerised system that will provide, after information on the enrolled participant is entered and inclusion criteria are verified, the patient's identification number and the allocated treatment.

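### The between-arm comparison of 12-month depression change is assigned to paired tests, which cannot compare two independent randomised groups

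*Protocol article*

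**What the plan says.** The Background of the protocol article gives secondary aim (a) as "to assess whether adding lithium has a specific impact in improving depressive symptoms". The Outcomes section lists the matching secondary outcome, "change in severity of depressive symptoms from baseline to endpoint and adverse reactions during the 12 months of follow-up".

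The Statistical analysis section defines two forms of it: "Change in severity of depressive symptoms from baseline to 12 months will be analysed as a continuous variable and as a dichotomous variables", the second being response, an improvement of at least 50%. It then states the comparison, "Change in severity of illness at 12-months will be compared between the two groups of treatment", and the method, presented as suited to repeated measurements: "paired t-test or McNemar non parametric test according to the variables distribution".

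On design, the abstract says "We will carry out a randomised, parallel group, assessor-blinded superiority clinical trial", and the Random allocation procedure section says "Patients will be randomly assigned to one of the two treatment groups with an equal probability of assignment to each treatment (allocation ratio 1:1". Allocation is stratified by presence or absence of an Axis II diagnosis. Nothing describes matching of patients or crossover.

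**The concern.** The stated purpose and the named tests do not fit together. The purpose is a contrast between two separate groups of patients. A paired t-test takes the mean of within-pair differences and tests it against zero. McNemar's test does the corresponding thing for a binary variable measured twice on the same unit. Neither uses the randomised allocation.

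At stake is secondary aim (a). If the sentence is followed, the trial learns whether depression scores fell over 12 months, which may happen in both arms for reasons unrelated to lithium. If it is not followed, the between-arm test has to be chosen outside what the article specifies.

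**Working it through.** **Step 1: can a pairing be found that makes the tests valid?**

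- *Across arms.* Patients are individually randomised 1:1 in permuted blocks within an Axis II stratum. No lithium patient is linked to a control patient, so there are no cross-arm pairs.
- *Within patients.* Baseline and 12-month QIDS do form a pair. The paired t statistic is the mean change divided by (SD of change / √n). It can be computed in each arm or on all patients together, but in neither case does treatment arm enter it.
- *Response.* Improvement of at least 50% is defined from baseline to 12 months, so a patient has one value of it and no baseline value. Setting everyone to non-responder at baseline would leave McNemar's test asking only whether anyone responded.

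**Step 2: does another sentence supply the between-arm test?**

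| Sentence in Statistical analysis | What it covers |
|---|---|
| Log-rank tests | Primary composite, all-cause mortality, suicide, DSH |
| Chi-square or Fisher's exact test | Suicide/DSH events; adverse reactions |
| Poisson regression with robust variance | Follows directly on the suicide/DSH comparison |
| Multivariate analyses | Prognostic factors; names no between-arm test |
| Paired t-test or McNemar's test | Depression change and response |

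None does. The other between-group comparisons in the section are given independent-sample tests.

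**Step 3: what happens if each arm is tested separately?** The article gives no power or SD for this outcome, so there is no figure to reproduce and the inputs are assumptions: two identical arms, SD of change σ = 6, n = 80 per arm, two-sided 0.05, common mean fall d.

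- Noncentrality: λ = d / (σ/√n), with 6/√80 = 0.671.
- p = probability that one arm's paired t-test is significant (noncentral t, n − 1 degrees of freedom).
- Probability that exactly one arm is significant: 2p(1 − p), since the arms are independent.

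| d | λ | p | 2p(1 − p) |
|---|---|---|---|
| 1 | 1.49 | 0.31 | 43% |
| 1.5 | 2.24 | 0.60 | 48% |
| 2 | 2.98 | 0.84 | 27% |
| 2.5 | 3.73 | 0.96 | 8% |
| 3 | 4.47 | 0.993 | 1.4% |

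The Power analysis section plans 105 per arm. With σ = 6 and n = 105 (6/√105 = 0.586), the same formula gives 48%, 40%, 14%, 2% and 0.2%.

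**Step 4: what happens when both arms improve more?** A simulation of 4,000 trials used 105 per arm, QIDS SD 5 at each visit and a baseline to 12-month correlation of 0.5. The SD of change is then √(25 + 25 − 2 × 0.5 × 25) = 5.

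| True falls (two arms) | Paired test, each arm | Paired test, all patients pooled | Two-sample test on change |
|---|---|---|---|
| 1 and 1 | 51% and 53% | 82% | 5.0% |
| 3 and 3 | 100% | 100% | 5.4% |
| 6 and 6 | 100% | 100% | 5.0% |
| 7 and 5 | 100% | 100% | 83% |

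The last row agrees with direct calculation: λ = 2 / (5 × √(2/105)) = 2.90, power about 82%. The paired tests give the same result whether the arms are identical (6 and 6) or differ by 2 points (7 and 5); the two-sample test separates the two cases.

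**The case against.** - *The detail belongs to a fuller analysis plan.* It would if the article had left the method open. It names two specific tests. The broader phrase about methods for repeated measurements does not help, because the parenthesis says which methods are meant.
- *McNemar's test may be meant only for the binary variable.* This is a fair reading: the preceding sentence defines a continuous and a dichotomous form, and the reference to distribution may be loose wording for variable type. On that reading McNemar's test is not offered as a substitute for a t-test on a skewed score. It still cannot compare the arms.
- *The harm is conditional.* This stands. A reader might infer that the trial will set a significant result in one arm against a non-significant one in the other, with a false-positive rate of 27% to 48%. The article does not say so; it states a between-group objective and attaches unsuitable tests. Those percentages also need small common falls and 80 per arm, a number the article does not give. At a fall of 3 points the disagreement is about 1% or less.
- *The outcome is secondary.* This also stands. The primary log-rank analysis and the sample size do not depend on this sentence.

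**Conclusion.** The sentence is wrong as written. The named tests cannot deliver the between-arm comparison it announces, and no other sentence supplies one for QIDS change or for response. That conclusion follows from the design and needs no numerical assumption.

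The size of the practical harm does rest on assumed SDs, sample sizes and mean falls. Across the settings above, with identical arms, disagreement between the two within-arm tests ranges from close to half of trials to almost none. Where disagreement vanishes, the problem becomes the opposite one: both arms are significant and nothing is learned about their difference. No single error rate should be attached to this point, and the documents do not support a claim that the trial's type I error is inflated by a given amount. The fault should be corrected because it removes the only stated test for a named aim, but it is confined to secondary aim (a).

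**What to change.** Replace the parenthesis with a between-arm method.

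- **Continuous change:** ANCOVA of 12-month QIDS on treatment arm, baseline QIDS and Axis II stratum. The minimum repair is a two-sample test on change from baseline.
- **Response:** the chi-square or Fisher's exact test that the section already uses for other outcomes, or Poisson regression with robust variance and the same covariates as the ANCOVA.

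Both can be run with the existing rule that carries the last depressive rating forward to 12 months. A mixed model on the monthly QIDS would also compare the arms, but it conflicts with that rule, so choosing it means changing the missing-data paragraph of the Statistical analysis section as well.

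The cost is wording only. Baseline and monthly QIDS scores and the Axis II stratum are already collected.

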### Statistical analysis

The statistical analysis will be masked, i.e. the trial biostatistician will be blinded to the treatment groups until the analysis has been completed. All analyses will be performed using Stata/SE, Release 11.1. Data lock will occur at 12 months, when data will be available for all participants. The pattern of missing values will be explored and interactions between treatment group and non-completers/completers will be examined with respect to demographic variables and baseline disease assessment.

The intention-to-treat (ITT) population, consisting of all subject randomly assigned to the competitive treatment strategies, will be used for the analysis of primary and secondary outcomes. Patients with missing values and patients lost during follow-up will contribute to the analysis of the primary and secondary outcomes only for the time during which data are available (censoring). Missing values in depressive symptom ratings will be imputed using the last observation carried forward (LOCF) approach: depressive ratings will be carried forward from the last available assessment to the 12-month follow up assessment. Additionally, patients in each arm will be always analysed according to the corresponding treatment group’s allocation at baseline.

In order to check the consistency of this ITT approach, the primary outcome will then be analysed using a per-protocol (PP) approach. The analysis of the PP population will be used for confirmatory purposes only. If less than 5% of patients switch from the allocated treatment to the competitive treatment, the PP analysis will not be performed.

Kaplan-Meier estimates for the time from randomised treatment assignment until the first event that constitutes the primary outcome will be plotted to compare the treatment’s effect, and log-rank test will be performed to test for differences. A Cox proportional hazard model will be used to explore the effect of possible confounding or interaction factors. Gender and age will be included into the model regardless of statistical significance criteria. The proportional hazard assumption of the effects will be tested. No interim analysis is planned for this trial.

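### The number of DSH acts is listed as a secondary outcome, but the chi-square or Fisher test fixed for it cannot analyse a repeatable count or use observed follow-up time

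*Protocol article*

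**What the plan says.** All references are to the protocol article.

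- **Outcomes** names the secondary endpoints: "As secondary outcomes, we will consider number of events (acts of DSH), number of suicides and all-cause mortality". The first is a count of acts, listed apart from suicides and deaths.
- **Statistical analysis** fixes the between-arm comparison: "The number of events/outcomes of interest (suicide or DSH) will be compared between the two groups of treatment through the chi-square test" (or Fisher's exact test). It continues: "When possible, a multivariate analysis will be performed through a Poisson regression model with a robust error variance".
- The same section gives a log-rank test for all-cause mortality and adds: "The same method will be applied for the following secondary outcomes: suicide mortality, deliberate self-harm".
- Its rule for incomplete data is that lost patients contribute to primary and secondary outcomes "only for the time during which data are available (censoring").
- **Baseline and follow up assessments** describes the data source: "Follow-up data will be obtained each month after random allocation using an electronic form". Any death or DSH is among the items collected.

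**The concern.** A chi-square or Fisher test on a two-arm table needs independent units, each counted once. A count of DSH acts does not have that form, because one patient may contribute several acts. The test can be made to run in two ways. It can use patients with at least one event, in which case second and later acts vanish. Or it can use acts, in which case repeats by one patient are treated as separate independent observations.

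The article itself gives reasons to expect repetition concentrated in some patients. Everyone enrolled has had a recent DSH episode. The Background calls the number of previous attempts the best predictor of further suicidal behaviour. Axis II comorbidity is permitted, and randomisation is stratified on it because it may affect the outcomes.

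Neither form of the test has a person-time term. A patient lost early without an act is counted like one followed for the full year, which is not what the article's own censoring rule says.

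At stake is the only listed outcome that measures the burden of repeated self-harm. It would be either unanalysed as defined or, on the act-level reading, tested with too small a standard error.

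**Working it through.** The article gives no figure for this outcome to reproduce: no repeat-act rate, no dispersion and no drop-out. The checks below therefore use assumed ranges, with 105 patients per arm as in the sample size section.

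**1. Which reading fits the text.** The sentence covers suicide as well as DSH, and suicide cannot recur. Fisher's test needs a non-event cell, which patients supply and act totals do not. The paragraph on adverse reactions uses the same tests for a proportion of patients. These point to a patient-level reading. Against that, the sentence speaks of a number of events, not of a proportion of patients, and Outcomes defines the first secondary endpoint as acts. The text does not settle the unit.

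**2. Patient-level reading: what is lost.** With mean m acts per patient and probability P of at least one act, the share of acts discarded is 1 − P/m. For negative binomial counts with shape k, P = 1 − (k/(k+m))^k and variance/mean = 1 + m/k.

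**3. Act-level reading: type I error.** Treating totals a and b as independent events uses z = (a − b)/√(a + b). If the true variance/mean ratio is φ, z has variance φ under no effect, so the rejection rate is about 2[1 − Φ(1.96/√φ)]. Example for φ = 1.6: 1.96/1.265 = 1.55, giving 12.1%.

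| m | k | φ | P | Acts discarded, patient-level | Type I error, act-level (formula) | Same (20,000-run simulation) |
|---|---|---|---|---|---|---|
| 0.30 | 1.0 | 1.3 | 23% | 23% | 8.6% | 8.3% |
| 0.30 | 0.5 | 1.6 | 21% | 30% | 12.1% | 11.8% |
| 0.45 | 0.5 | 1.9 | 27% | 39% | 15.5% | 15.2% |
| 0.45 | 0.3 | 2.5 | 24% | 47% | 21.5% | 21.6% |
| 0.60 | 0.3 | 3.0 | 28% | 53% | 25.8% | 25.1% |

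Formula and simulation agree. Without overdispersion (φ = 1) the act-level error is the nominal 5%.

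**4. Second simulation, including unequal follow-up.** This used 4,000 runs under no effect. P over 12 months was set at 35% (the article's control rate) or 22.5% (the average of its 35% and 10%). Between-patient variance of the act rate was 0, 1, 2 or 4.

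- *No loss.* The patient-level test rejects in 4.4–5.4% of runs, so it keeps its level. It discards 12–19% of acts at variance 0 and 49–70% at variance 4.
- *Loss of 40% in one arm and 10% in the other, at uniform times.* Mean exposure is 1 − 0.40 × 0.5 = 0.80 of a year against 1 − 0.10 × 0.5 = 0.95. The patient-level test now rejects in 8–12% of runs and the act-level test in 10–46%.
- *Rate ratio with patient-level robust variance and a person-time offset.* It rejects in 4–7% of runs throughout.

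**5. Do the neighbouring analyses fill the gap?** The log-rank test for DSH respects censoring, but it analyses time to an event and not how many acts follow. The Poisson model with robust variance could handle clustering if its response were acts per patient. The article makes it conditional and multivariate and names neither a count response nor an offset. The same model is also commonly fitted to yes/no outcomes to obtain risk ratios, which would again drop repeats.

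**The case against.** The best defence is that the sentence was meant at patient level throughout. Chi-square or Fisher followed by robust-variance Poisson regression is the familiar pairing for a binary outcome, and with equal follow-up that test keeps its 5% level. DSH also has a log-rank analysis that applies the promised censoring, and a model able to handle repeat acts is already named. Whether its response is a count, and whether it carries an offset, could be left to an analysis plan that is not shown.

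Much of this stands. Three stronger readings that a reader might infer are not supported:

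- *That the plan will produce false positives at up to 25%.* This applies only to the act-level reading, which is the less likely one. It also depends on an assumed dispersion, and the mildest case in the table gives about 8%. Nothing in the article says that acts will be treated as independent.
- *That the planned analysis of DSH ignores unequal follow-up.* The log-rank test handles it for time to DSH. The defect is confined to the comparison of numbers.
- *That clustering is overlooked altogether.* The robust-variance Poisson model could accommodate it, though the article does not commit to that use.

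What the defence does not remove is the mismatch itself. If the sentence is at patient level, the count in Outcomes has no committed analysis. This is a stated method unsuited to a stated outcome, not a detail left for later.

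**Conclusion.** The point holds as a defect in one secondary analysis. On the likelier patient-level reading, the fault is that a different question is answered: across the scenarios tried, 12–70% of acts are discarded, while type I error stays near 5% when follow-up is equal. On the less likely act-level reading, type I error is about 8–25% for a variance/mean ratio of 1.3–3.0.

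On both readings the test conflicts with the article's censoring rule. The practical harm from that arises mainly if loss differs between arms. The 8–12% found for the patient-level test rests on a deliberately large imbalance, 40% against 10%, for which the article offers no basis. All dispersion and loss values here are assumptions.

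The primary time-to-first-event log-rank analysis is untouched. The change is worth making, but the trial's main conclusion does not depend on it.

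**What to change.** In Statistical analysis, state that the number of committee-validated DSH acts per patient is compared between arms by Poisson regression with robust variance, the model already named, or by negative binomial regression. Include log follow-up time as offset and report a rate ratio with 95% CI. Make this the committed main comparison for that outcome, not a conditional addition. Reserve chi-square or Fisher for the proportion of patients with at least one event, and say so in those words.

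The cost is analysis wording only. The article does not describe separate fields for the count and date of each act. However, DSH is reported monthly, the committee reviews every reported hazardous act, and the log-rank analysis needs event times, so the acts per patient and the time observed should be obtainable from data the trial must already hold. Sample size and primary analysis do not change.
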